#### Secondary outcomes

We will repeat the mixed multilevel models, and the calculation of Cohens’ *d*, for all outcomes of parental well-being. Next, to determine the effect of the intervention on the quality of caregiving after birth, we will add higher-quality caregiving as a secondary outcome variable to the model. Furthermore, to test whether prenatal well-being of the parents influences postpartum caregiving quality, we will use parental well-being (measured at 26 and 34 weeks of pregnancy) as a predictor of higher-quality caregiving. Finally, we will determine the effect of prenatal parental well-being on infant outcomes postpartum (mediated by higher-quality caregiving). For each of the outcomes we will calculate the between-group effect size at t3 and t4 and their 95% confidence interval. Gender will be added as an interaction term to the model, to see if there are differences between mothers and fathers.

Demographic data, attachment style of the parents and data related to the delivery and birth (birth weight, Apgar score, spontaneous delivery, caesarean section, birth complications) will be used as control variables in the model.

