## Abstract

**Background:**

The first months after birth can be challenging for parents, leading to parental distress and decreased well-being. Parents with high levels of distress are found to respond less adequately and sensitively to their infant, which in turn affects infant well-being and health. The goal of this study is to examine the effectiveness of a psycho-educational intervention to prevent postpartum parental distress and enhance the quality of caregiving and infant well-being. In contrast to other interventions, this intervention will be (1) offered already before birth, (2) offered to all parents-to-be, regardless of their risk of postpartum distress, and (3) include fathers. The proposed study examines the effectiveness of this intervention on (1) parenting distress, (2) quality of caregiving, and (3) the infant’s well-being.

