**Fig. 2 Fig2:**
[figure not shown]
Standard Protocol Items: Recommendations for Interventional Trials (SPIRIT) Figure with trial design and outcome assessments. After screening for eligibility, participants are asked to sign an informed consent form and to complete the baseline questionnaire. Then, participants are randomized in either the intervention or the control group. The intervention starts with a home visit (at t1) and a postnatal telephone call (4 weeks after birth). Measurements take place at 26–34 weeks of pregnancy (baseline; t0); 34–36 weeks of pregnancy (t1); 2 weeks after birth (t2; delivery characteristics); 6 weeks after birth (t3); and 10 weeks after birth (t4)

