### Intervention

Parents will receive access to the psycho-education materials (booklet and video) directly after randomisation, which is between the 26th and the 34th weeks of pregnancy (depending on when the parents apply for participation). The intervention further consists of two support sessions: one home visit between 34 and 36 weeks of pregnancy and one telephone call 4 weeks after birth.

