
##### Quality of caregiving

Quality of caregiving will be measured by assessing the bonding between parent and child, the duration of breastfeeding, and the duration of room-sharing at 10 weeks postpartum.Bonding will be measured with the Maternal Postnatal Attachment Scale (MPAS; [14, 59]). This scale consists of 19 statements referring to parent-child relationship. Each statement can be answered on a 2-point; 4-point; or 5-point scale. An example item is:“When I am with the baby, I feel tense and fearful.” Total scores range from 19 to 95 and can be computed by summing up individual item scores. Low total scores indicate bonding problems between parent and child. Van Bussel et al. [59] reported a Cronbach’s alpha of .75 of the MPAS when administered 8–12 weeks after birthBreastfeeding will be assessed by measuring the duration (in weeks) of breastfeeding and/or breastfeeding mixed with bottle-feedingRoom-sharing will be measured as the duration (in weeks) of room-sharing (the infant sleeps in the room of the parents at night)

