#### Infant well-being and health

The well-being of the infant will be measured through a diary (72 h at 6 weeks postpartum) assessing crying, sleeping, and feeding [6]. Parents are supposed to rate precision in 5-min slots using different symbols. The following behaviors will be assessed: asleep, awake, and being content, awake and being fussy, awake and crying, awake and feeding; awake and sucking (thumb/dummy). Parents can also indicate the time and duration of feeding, and the type of feeding (breastmilk (through breastfeeding or bottle) or formula milk). Parents are asked whether the rated 72 h period can be viewed as a “typical” period or not. Furthermore, we will ask parents at 6 and 10 weeks after birth whether they are experiencing a problem with infant sleep (day or night), crying or feeding, and if so, to rate the severity of this problem on a 7-point Likert scale ranging from 1 (hardly any problem) to 7 (a severe problem) [27]. Infant health is measured in terms of somatic indices and somatic problems (at 6 and 10 weeks after birth). Parents are asked about their infant’s weight, length, and head circumference and will also be asked to indicate whether their child has experienced fever, a runny nose, any coughing, ocular inflammation, or diaper rash. Additionally, parents are asked if their child had experienced some other medical condition and whether their child has been using any medication.

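### The only model described for infant outcomes takes non-randomised prenatal parental well-being as exposure without naming arm, and for the 6-week outcomes its caregiving mediator is assessed later, at 10 weeks

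*Protocol article*

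**What the plan says.** The abstract sets three aims: "The proposed study examines the effectiveness of this intervention on (1) parenting distress, (2) quality of caregiving, and (3) the infant’s well-being". The Objectives section lists infant well-being and health among the secondary outcomes.

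Under Statistical analysis, Secondary outcomes, the protocol repeats the mixed model for parental well-being and adds caregiving quality to it in order to estimate the intervention effect. It then turns to a different explanatory variable: "we will use parental well-being (measured at 26 and 34 weeks of pregnancy) as a predictor of higher-quality caregiving". For infants it says: "Finally, we will determine the effect of prenatal parental well-being on infant outcomes postpartum (mediated by higher-quality caregiving"). The next sentence promises, for every outcome, a between-group effect size with 95% confidence interval at t3 (6 weeks) and t4 (10 weeks).

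On timing:
- The Fig. 2 caption places the baseline questionnaire first. "Then, participants are randomized in either the intervention or the control group".
- The Intervention section says: "Parents will receive access to the psycho-education materials (booklet and video) directly after randomisation".
- The Quality of caregiving section lists bonding, "the duration of breastfeeding, and the duration of room-sharing at 10 weeks postpartum".
- The Infant well-being and health section says: "The well-being of the infant will be measured through a diary (72 h at 6 weeks postpartum) assessing crying, sleeping, and feeding". Sleep, crying and feeding problem ratings and infant health are collected at both 6 and 10 weeks.

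**The concern.** A trial that aims to show an effect on infants should specify its main infant analysis around the randomised contrast. Here the one model spelled out for infants has an observational exposure. Its coefficient describes how parents who felt better before birth differ from those who felt worse. It is nevertheless called an effect, in a trial report where readers may take it as evidence about the intervention.

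The mediation step adds a second problem for the 6-week outcomes. A baby who cries heavily at week 6 may change how the parent bonds, feeds or arranges sleep by week 10. The protocol's own Background notes that breastfeeding and room-sharing are often stopped in the first two months. An association between the two could then be reported as caregiving explaining crying when the influence ran the other way.

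**Working it through.** **The plan's own figure.** The point rests on no figure, but the sample size is used below, so it is reproduced first. Inputs from Sample size calculation: d = 0.50, power 80%, alpha 0.05 (taken as two-sided, which the protocol does not state).

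n per arm = 2(z₀.₉₇₅ + z₀.₈₀)²/d² = 2(1.960 + 0.842)²/0.25 = 62.8, so 63. The two-sample t-test gives 63.8, so 64, with power 80.1% at 64. The stated 64 per arm and 128 in total are reproduced.

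**Timing side by side.**

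| Quantity | Role in the stated infant model | When measured |
|---|---|---|
| Parental well-being, t0 | exposure | 26–34 weeks of pregnancy, before randomisation |
| Parental well-being, t1 | exposure | 34–36 weeks, after access to booklet and video |
| Bonding, breastfeeding duration, room-sharing duration | mediator | 10 weeks after birth (natural reading) |
| Diary: crying, sleeping, feeding | outcome | 6 weeks only |
| Problem ratings, infant health | outcome | 6 and 10 weeks |

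**What follows.**
1. The t0 score cannot carry any intervention effect, because it precedes allocation.
2. The t1 score can carry part of one (booklet, video, possibly the home visit held in the same window) but never the telephone call 4 weeks after birth. The two scores together mix pre- and post-randomisation information.
3. For 6-week outcomes the mediator is assessed 10 − 6 = 4 weeks after the outcome. Bonding wholly postdates them. The two durations describe behaviour from birth onward, so only the part covering weeks 6 to 10 postdates them.
4. For 10-week problem ratings and health items the mediator does not come after the outcome.
5. The diary has no t4 value, so the effect size promised for every outcome at t4 cannot be computed for it.

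**Illustrative simulation.** The coefficients are assumed and none come from the protocol. There were 128 infants, 64 per arm, and 1,000 runs per scenario. Well-being at t0 is standard normal and t1 correlates 0.7 with it. The infant outcome and caregiving each have residual SD 1, caregiving depends on t0 well-being with slope 0.3, and caregiving never affects the infant outcome. The regressions are simple and leave out the planned control variables. The mediation test is joint significance of both paths. Entries are the share of runs with p < 0.05.

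| Scenario | t0 predictor | t1 predictor | Arm | Mediation |
|---|---|---|---|---|
| A: arm effect 0.5, not through well-being | 4.6% | 5.3% | 81.7% | 4.7% |
| B: no arm effect, well-being slope 0.4 | 99.5% | 84.8% | 4.7% | 4.9% |
| C: as B, and the outcome drives later caregiving (0.4) | 99.2% | 85.1% | 4.7% | 98.8% |

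In A the stated predictor misses a real arm effect. In B it is significant with no arm effect. From B to C, letting the outcome influence later caregiving raises the false mediation rate from 4.9% to 98.8%. These rates show direction and do not estimate this trial's bias.

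**What an arm comparison would give.** With 64 infants per arm and complete data, power is 80.1% at an assumed d = 0.5. The 95% interval half-width for d is 1.96·√(2/64 + d²/(2·128)), which is 0.346 at d = 0 and 0.352 at d = 0.5.

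**The case against.** A reader might infer that infants are analysed by parental well-being in place of randomised arm. The protocol does not support that. The sentence after the mediation plan promises between-group effect sizes with 95% confidence intervals for every outcome, infant outcomes are among the named outcomes, and the analysis is by intention to treat. An interval of that kind already shows whether the arm difference excludes zero. A condensed article may also leave the exact regression to a fuller plan. This part of the objection stands, and an unnamed regression would not by itself be a finding. What remains is that the model the article does state has an exposure that does not match the stated aim.

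A reader might also infer that the whole infant mediation analysis is reversed in time. That is too broad. The 10-week outcomes are unaffected, and the two durations contain usable information from before week 6. The 10-week timing could also be read as attaching to room-sharing alone, and the schedule figure is not shown. For the same reason it cannot be said flatly that no caregiving measure exists at 6 weeks.

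The mediation analysis can fairly be seen as testing the hypothesised chain from parents through caregiving to infants, with demographics, attachment style and birth data as control variables, and arm may be kept in the model. Adjustment reduces confounding but does not make the exposure randomised, and it does not correct the time order. A t1 score has a legitimate place in such a chain provided it is not treated as a baseline.

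**Conclusion.** The point holds in a limited form. A randomised comparison of infant outcomes is planned, but the only model described for them does not name arm and has a non-randomised exposure, part of it measured before and part after randomisation. That model cannot answer the third stated aim. Mediation through bonding, and through durations that run into weeks 6 to 10, has the wrong time order for the diary and the other 6-week infant outcomes.

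The fault reaches secondary outcomes only and leaves the primary analysis untouched. Its numerical size cannot be derived from the protocol. The conclusion assumes that all three caregiving measures are assessed at 10 weeks, which is the natural reading of the Quality of caregiving section. If some were also taken at 6 weeks, the time-order part would weaken and the point about the exposure would stand.

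**What to change.** - **Main infant analysis.** For each infant outcome, state a model with randomised arm as the exposure. Report the arm difference with 95% confidence interval, adjusted for baseline covariates, at the occasions when the outcome is measured: diary at t3, problem ratings and health items at t3 and t4. Correct the sentence on effect sizes at t3 and t4 so that it does not promise a t4 diary result.
- **Well-being and mediation analysis.** Label it exploratory and include arm in it. Use only mediators that precede the outcome, for example breastfeeding or room-sharing status up to week 6, derived from the recorded durations, against t4 infant outcomes. This assumes that durations are counted from birth. Do not mediate 6-week outcomes through 10-week bonding.
- **The t1 score.** If it is kept as a predictor, describe it as a post-randomisation variable and not as a baseline.

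The cost is revised wording and a little more analysis, using data already being collected. Mediation of the 6-week outcomes through 10-week caregiving is given up.

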### Sample size calculation

We expect an effect size of 0.50 (Cohen’s *d*). This is based on the work of Hiscock et al. [27]. Their intervention, aimed at preventing infant sleep and crying problems, showed an odds ratio of 0.57 (converted into a Cohen’s *d* of 0.48) on symptoms of maternal depression in favor of the intervention group. Using a power of 80%, an alpha of 0.05, we need to include 64 participants in both conditions, 128 in total, to answer our primary research question.

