### Randomization

An independent researcher will generate random number sequences using random allocation software with a 1:1 ratio. We will use random sequence blocks (blocks between 6 and 8), stratified by birth order (first child/ no first child) and paternal participation (yes/no). An independent researcher will allocate each consenting participant to either the control or the intervention group. Given the nature and design of the study, blinding after randomization is not possible. Participants will receive the outcome of randomization by e-mail. Please refer to Fig. 3 for an overview of participant's flow through the study.

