##### Parental well-being

Parental well-being is defined as: (1) depressive symptoms, (2) symptoms of anxiety, (3) satisfaction with the parental role, (4) parental self-efficacy, and (5) sleep quality and quantity.Depressive symptoms will be measured with the Edinburgh Postnatal Depression Scale (EPDS; [17]; Dutch translation Pop, Komproe, and Van Son, 1992). This scale consists of 10 items. Participants can indicate the experienced frequency of each depression-related statement on a 4-point scale. Items are scored 0, 1, 2, or 3 (items 3, 5, 6, 7,8, 9, and 10 are reverse scored). Total scores range from 0 (no depressed feelings) to 30 (severely depressed feelings). The scale shows good psychometric properties: Pop et al. [45] reported an internal consistency of .82 (Cronbach’s alpha) and sufficient concurrent validitySymptoms of anxiety will be measured with the seven items of the anxiety subscale of the Hospital Anxiety and Depression Scale (HADS; [42, 51]). For each item, participants can indicate on a 4-point scale how much anxiety they experience. Total scores on the anxiety subscale vary from 0 (no anxiety) to 21 (severe anxiety). Spinhoven et al. [51] reported good psychometric properties for the Dutch versionSatisfaction with the parental role will be measured with three items of the Dutch translation of the Parenting Stress Index (PSI; [18, 19, 36]). Following the procedure of Missler et al., [39], four items were added to this scale. Adding items was necessary because to our knowledge, no measure of parenting satisfaction currently exists. We thus decided to use this composed scale. An example item is: “I enjoy spending time with my child.” For the administration before birth (t0 and t1), the items were rephrased such that the expectation of parents of their satisfaction with their new role after the birth of their child became central: “I expect I will enjoy spending time with my child”Parents will be asked to rate their efficacy as a parent on a 5-point scale, ranging from 1 (not very good) to 5 (a very good parent; [16, 27, 49])Sleep quality and quantity is measured with two items of the Pittsburgh Sleep Quality Index (PSQI; [12]) adapted by [16]. The quality item is: “Over the last 2 weeks, how would you rate your own sleep quality?” Response options are: “Not nearly good enough”; “Not quite good enough”; “Good enough”; and “More than good enough.” The quantity item is: “Over the last 2 weeks, how would you rate your own sleep quantity?”, with the following response options: “Not nearly enough”; “Not quite enough”; “Enough”; and “More than enough.”

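### The control variables named for the secondary outcome models omit each parent's own t0 score of the outcome analysed, which gives up precision that the trial could probably have at no cost

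*Protocol article*

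**What the plan says.** All places are in the protocol article.

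- **Statistical analysis, Secondary outcomes.** The mixed multilevel model of the primary outcome is repeated for every parental well-being outcome. The section ends with a list of covariates: "Demographic data, attachment style of the parents and data related to the delivery and birth", with five delivery and birth variables spelled out, which "will be used as control variables in the model". No earlier score of the outcome is listed.
- **Same section.** Prenatal well-being does have a use: "parental well-being (measured at 26 and 34 weeks of pregnancy) as a predictor of higher-quality caregiving", and then as a predictor of infant outcomes through caregiving. Adjusting the arm comparison on postpartum well-being is not mentioned.
- **Statistical analysis, Primary outcome.** The one nesting level named is the couple. No time term, baseline term or constraint on baseline means is described. Cohen's d comes from the raw difference in means over the pooled standard deviation.
- **Parental well-being.** "Parental well-being is defined as: (1) depressive symptoms, (2) symptoms of anxiety", followed by role satisfaction, self-efficacy and sleep. Depression is measured with the EPDS and anxiety with the HADS anxiety subscale.
- **Legend of Fig. 2.** The baseline questionnaire is completed first, and randomisation follows.

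**The concern.** The earlier score on the same scale is usually among the best available predictors of a later score. The article specifies covariates down to the Apgar score yet leaves this one out. Attachment style and demographics can stand in for it only in part. Randomisation is stratified by birth order and paternal participation, so baseline mood is not balanced by design.

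At stake is the width of the confidence intervals for the t3 and t4 effects on depression, anxiety and the other well-being scales. The sample size was set for the primary question only, so these comparisons have no stated reserve of precision. If the choice is not fixed before analysis, it also remains open whether adjusted or unadjusted results are reported.

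**Working it through.** **1. Is the t0 score available?** The Secondary outcomes analysis section says parental well-being is measured at 26 and 34 weeks of pregnancy. The Parental well-being section counts depressive and anxiety symptoms as its first two components. Together these place the EPDS and HADS at t0, and the Fig. 2 legend places t0 before randomisation. Three facts keep this an inference:
- neither scale has its own time points in the text;
- the schedule figure is not shown;
- the Objectives list anxiety and depression as parental distress, apart from well-being, which there means role satisfaction and self-efficacy.

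**2. The plan's own figure.** Inputs from Sample size calculation: "We expect an effect size of 0.50" and "Using a power of 80%, an alpha of 0.05, we need to include 64 participants in both conditions, 128 in total". From Randomization: "random allocation software with a 1:1 ratio". The two-sided normal formula gives 63 per arm, and the t-test gives 63.8, hence 64. A one-sided test would give 50, so the figure is two-sided. It is a comparison of two postpartum means without baseline adjustment. Power at 64 per arm is 80.7% (normal) or 80.1% (t-test).

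**3. Effect of adding t0.** Let ρ be the correlation of the t0 score with the postpartum score. Adjustment multiplies the residual variance by 1 − ρ², so

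SE = √(2/64) × √(1 − ρ²) = 0.177 × √(1 − ρ²) in SD units, and power = Φ(d/SE − 1.96).

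The article gives no ρ, so the values below are assumptions. The d of 0.50 is the planned value for the primary outcome, used here only as an illustration.

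| ρ (assumed) | variance factor | fall in SE | equivalent N (128 / factor) | power at d = 0.50 |
|---|---|---|---|---|
| 0 | 1.00 | – | 128 | 80.7% |
| 0.2 | 0.96 | 2.0% | 133 | 82.3% |
| 0.3 | 0.91 | 4.6% | 141 | 84.3% |
| 0.4 | 0.84 | 8.3% | 152 | 87.0% |
| 0.5 | 0.75 | 13.4% | 171 | 90.4% |
| 0.6 | 0.64 | 20.0% | 200 | 94.2% |

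**4. Allowing for the covariates already listed.** If they explain a share R² of the variance, the residual variance is (1 − R²)(1 − ρ²), with ρ now the partial correlation. R² is also an assumption. The variance factor for adding t0 is unchanged at a given partial ρ, but the starting power is higher:
- R² = 10%: power goes from 84.6% to 87.8% (partial ρ 0.3) or 93.1% (0.5).
- R² = 20%: power goes from 88.5% to 91.2% (0.3) or 95.5% (0.5).

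**5. Would a mixed model recover the gain anyway?** A simulation of 4,000 trials with 64 per arm compared four estimators. The correlation was taken as known for the last.

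| ρ | postpartum only | t0 as covariate | change from t0 | t0 as response, arms equal at t0 |
|---|---|---|---|---|
| 0.3 | 0.177 | 0.169 | 0.208 | 0.168 |
| 0.5 | 0.175 | 0.152 | 0.177 | 0.152 |
| 0.7 | 0.176 | 0.128 | 0.139 | 0.128 |

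Entries are empirical standard errors. The change contrast has variance factor 2(1 − ρ), for example 1.4 at ρ = 0.3, and stays above the covariate model throughout. Only the version with equal baseline means matches it, and the article describes no such model.

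**The case against.** The strongest case against has five parts.

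- **Collection at t0 is not documented scale by scale.** Under the narrower definition in the Objectives, the sentence on prenatal well-being says nothing about depression or anxiety. This stands as a limit. A reader might take it as established that a like-for-like EPDS and HADS baseline exists. The documents support that only by joining two sections.
- **The list may be meant mainly for the caregiving and infant models.** It closes the section after those analyses and refers to one model, and attachment style is justified elsewhere by its effect on caregiving. The scope is indeed unclear. But the paragraph falls under a heading that covers all secondary outcomes, and nothing restricts it.
- **The mixed model may already use t0 as a response.** The article does not exclude this, so the stronger inference that the plan never uses t0 in the arm comparison is not supported. What stands is that no such use is described, and that only one form of it removes the loss.
- **The size is assumed.** Pooling mothers and fathers, the listed covariates, and the exclusion of women with current or recent treatment for psychopathology all bear on the relevant partial correlation. The exclusion may lower it. At 0.2 to 0.3 the gain is small. Quoting a 16% to 36% cut as the likely gain would presume a correlation of 0.4 to 0.6.
- **Nothing is biased or miscalculated.** This is correct. Randomisation protects the unadjusted contrast, chance imbalance is reflected in its confidence interval, and the 80% power claim covers the primary question only.

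**Conclusion.** The point holds as a free improvement. The article fixes a covariate list for the secondary outcomes that omits the t0 score of the outcome analysed, and describes no model that would use t0 to adjust the arm comparison. The cost is precision only: a variance of the arm contrast larger than it need be. Adjustment would remove 9% to 36% of it if the partial correlation after the listed covariates is 0.3 to 0.6.

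Two assumptions carry this: that the EPDS and HADS anxiety scores are taken at t0, and the range of the correlation, which the article does not give. A reader might infer that the planned comparisons are invalid, or that the trial is underpowered for this reason. Neither follows. The contrasts are between randomised arms, and the sample size figure reproduces as stated. The point also does not extend to the primary stress score, whose prenatal items are rephrased as expectations and whose time points are a separate matter.

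**What to change.** In Statistical analysis, Secondary outcomes, choose one of two equivalent statements:

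1. Add each parent's own t0 score of the outcome analysed (EPDS, HADS anxiety, and any other well-being scale collected at t0) as a covariate in the model for the t3 and t4 arm contrasts, with t0 not also a response.
2. State a repeated-measures model that includes t0 as a response and sets the arm means equal at baseline.

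The two should not be combined, since the same score would then stand on both sides of the model. Report the adjusted t3 and t4 effects with their 95% confidence intervals. In the same edit, state in the text which well-being scales are collected at t0.

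The cost is a sentence or two, written before the analysis. If the scores are collected at t0 as the text indicates, no new data are needed. Adjusting for a score taken before randomisation introduces no bias.

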#### Birth

Variables related to the delivery and the birth are assessed 2 weeks after birth: birth weight, Apgar score, spontaneous delivery, caesarean section, birth complications. We will test whether there are differences between the intervention and control groups for these variables (measuring possible stress factors during the delivery) in the analyses.

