### Statistical analysis

The study will be conducted in adherence to the Consolidated Standards of Reporting Trials (CONSORT) Statement. We will perform intention-to-treat analysis, in which all patients who are randomized will be analyzed (independent of treatment or study completion), as well as completers-only analyses. Completers are defined as participants who completed all measurements. Baseline data will be explored to see if there are differences between the group that remains in the study and the group that drops out.

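### Delivery and birth variables recorded after randomisation are planned as control variables in the secondary models, and can bias the intervention effect if assignment influences them

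*Protocol article*

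**What the plan says.** The sentence at issue closes the account of the secondary analyses (Protocol article, Statistical analysis, Secondary outcomes). It puts demographics, attachment style and delivery data in one covariate list, and of the last group says "data related to the delivery and birth (birth weight, Apgar score, spontaneous delivery, caesarean section, birth complications) will be used as control variables". It does not separate variables fixed before randomisation from those that arise later, and it does not call the adjustment exploratory.

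The timing comes from other sections of the article:

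- **Baseline variables:** demographics and attachment style are taken at t0.
- **Intervention:** "Parents will receive access to the psycho-education materials (booklet and video) directly after randomisation", at 26–34 weeks of pregnancy. The home visit is at 34–36 weeks and the telephone call four weeks after birth.
- **Birth:** delivery data are collected at t2, two weeks after birth, and "We will test whether there are differences between the intervention and control groups for these variables (measuring possible stress factors during the delivery".
- **Primary outcome (assessments):** maternal parenting stress is scored at t0, t1, t3 and t4, so not at t2.

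The Statistical analysis section promises an intention-to-treat analysis in which "all patients who are randomized will be analyzed (independent of treatment or study completion". The text on the primary analysis names group, parental sex and their interaction, lists no control variables, and relies on the mixed model being robust to missing data. The article does not address missing covariate values.

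**The concern.** Randomisation balances what is fixed before it. A covariate measured afterwards can itself be a result of assignment. Conditioning on it then does two things to the group coefficient. It removes whatever part of the effect runs through that covariate. It also introduces bias through causes shared by the covariate and the outcome, because parents with the same delivery experience are no longer exchangeable between arms.

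The stated objective is the effect of the intervention after birth, that is, the total effect of being offered it. A model adjusted for delivery variables may answer a different question.

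A second issue concerns who is analysed. Likelihood-based mixed models cope with missing outcomes, but a record with a missing covariate normally drops out of the fit. A mother who misses only the t2 questionnaire has every stress score, yet she would be lost from any model that carries the delivery covariates.

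**Working it through.** **1. Order of events.** Randomisation and access to materials (26–34 weeks) → home visit (34–36 weeks) → birth → delivery data (t2, 2 weeks) → telephone call (4 weeks) → outcomes at t3 (6 weeks) and t4 (10 weeks). Every component except the call precedes t2, so the delivery variables are post-randomisation and lie between most of the intervention and the outcomes.

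**2. The plan's own figure.** The article states "We expect an effect size of 0.50" and "Using a power of 80%, an alpha of 0.05, we need to include 64 participants in both conditions, 128 in total", with 1:1 allocation. Taking alpha as two-sided (the article does not say):

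- Normal approximation: n per arm = 2 × (1.960 + 0.842)² / 0.50² = 62.8, so 63.
- Exact two-sample t-test: 63.77, so 64 per arm, with power 80.1%.

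The sample size reproduces and is not in dispute. It serves only as a reference point below.

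**3. Effect of adjusting.** In a linear model, adjusted effect = total effect − g × s. Here g is the effect of assignment on the covariate, in SD, and s is the within-arm slope of the outcome on that covariate. The article gives neither. Assume s = 0.3, g from 0 to −0.3 (assignment lowers delivery stress), one continuous covariate, and a total effect of −0.50:

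| g | −0.50 − g × 0.3 | Adjusted effect |
|---|---|---|
| 0 | −0.50 − 0 | −0.50 |
| −0.1 | −0.50 + 0.03 | −0.47 |
| −0.2 | −0.50 + 0.06 | −0.44 |
| −0.3 | −0.50 + 0.09 | −0.41 |

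At g = −0.2 the change is 0.06 / 0.50 = 12%. A shift in the opposite direction would exaggerate the effect by the same amount.

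A simulation with 1,000,000 records gave −0.501, −0.471, −0.439 and −0.410 when the covariate itself drove the outcome. In a second version the covariate had no effect on the outcome but shared a cause with it, with the same slope (0.6 × 0.5 = 0.3). The adjusted estimates were −0.493, −0.467, −0.439 and −0.406, against unadjusted estimates of −0.493, −0.497, −0.497 and −0.495. In that version nothing passes through the covariate, so the shrinkage is pure bias. In both versions it vanishes at g = 0.

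**4. Missing t2 data.** The article gives no rate. Assume 5–20% of 64 per arm lack t2 data and are dropped (two-sided t-test, d = 0.50):

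| Missing | Women left | Power |
|---|---|---|
| 0% | 128 | 80.1% |
| 5% | 122 | 78.2% |
| 10% | 116 | 76.1% |
| 15% | 108 | 73.1% |
| 20% | 102 | 70.6% |

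These figures are for a simple comparison of mothers at one time point. The planned multilevel model with both parents would differ somewhat.

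**The case against.** There is a fair case on the other side.

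- **Scope.** The sentence stands under Secondary outcomes, and the primary model is described without control variables. A reader might infer that the primary analysis of maternal stress is adjusted for delivery. The article does not say so. Its singular reference to the model could cover all analyses, the secondary effect models, or only the non-randomised questions in the same section (prenatal well-being as a predictor, and mediation). This limit stands.
- **No demonstrated pathway.** The booklet covers responding, crying, feeding and sleeping, and no childbirth content is described. A reader might take the planned between-arm test of delivery variables as a sign that the sponsor expects an effect on them. Similar wording is used for marital satisfaction, so it reads more naturally as a comparability check. The shift may be nil, and then adjustment causes no such bias and gains some precision. This stands, so the bias is conditional. Reporting is still a possible route: parents are unblinded and assessments are online, so if complications are parent-reported, the arms could differ in reports without differing in deliveries.
- **An unadjusted contrast is planned.** Cohen's d is built from raw means and the pooled SD. That is true and useful, but it does not repair the model-based test, which is the main inference.
- **Missing covariates.** A reader might conclude that the plan contradicts its own intention-to-treat statement. It does not state a complete-case rule. The loss follows from usual software behaviour, and imputation may be set out in an analysis plan that is not shown. This point therefore holds only conditionally.

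**Conclusion.** The concern holds in a limited, conditional form and should be fixed. The article commits the secondary models to adjusting for variables that arise after randomisation and after most of the intervention. If assignment affects those variables or their reporting, the group coefficient departs from the total effect; if not, it does not. Under the assumed inputs the departure runs from nothing to 0.09 on an effect of 0.50. The documents supply neither the shift nor the slope, and 0.50 is the planning value for the primary outcome, used here only as a scale.

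The loss of participants depends on how missing covariates are handled. If they are not imputed, an assumed 5–20% missing at t2 would work against the aim of analysing everyone randomised and would cost roughly 2 to 10 percentage points of power in a simple comparison.

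The documents do not establish that the primary analysis is affected. They leave it open, and that should be settled in the text.

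**What to change.** Replace the covariate sentence with a rule that every model estimating the intervention effect adjusts only for variables measured before randomisation, such as demographics and attachment style at t0, and state that the rule also applies to the primary model. Summarise delivery and birth variables descriptively by arm. If a delivery-adjusted analysis is wanted, label it exploratory, keep it out of the effectiveness claim, and say how missing t2 values are handled in it.

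The cost is one or two sentences and a little explained variance. In the illustration with slope 0.3 and no shift, adjusting would sharpen the effect to 0.50 / √(1 − 0.3²) = 0.524 and raise power from 80.1% to 83.7%, with no t2 data missing. That gain is given up, but it exists only if assignment leaves delivery untouched; with a 0.2 SD shift the adjusted analysis would have 73.5% power. The article reports recruitment as ongoing, so on its account the change could be made before the arms are compared.
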